### Data and Safety Monitoring Board

A data and safety monitoring board (DSMB) will be set up for this research project to review trial data at regular intervals. The members of the DSMB will be independent to the clinical researchers actively working on the project. The planned DSMB members include a statistician from Curtin University, an academic working (with experience in BC research) from an interstate university and a BC consumer advocate.

### Adverse event reporting

Non-minor adverse events will be reported to the HREC within 48 hours.

### Follow-up of Adverse Events

We will report any adverse events to the treating medical team as appropriate.

## 9 Data Management, Statistical Analysis and Record Keeping

## Statistics and Interim Analysis

*The primary research questions for this study are:*

- Does the SMART program, compared with usual care, change health-related quality of life (primary outcome) measured 16-weeks and 12-months following randomisation?

AND

- Does the SMART program, compared with usual care, change peripheral muscle strength, muscle mass, exercise tolerance, exercise adherence and chemotherapy completion rates (secondary outcomes) measured 16 weeks following randomisation?

The analyses for this research question will be performed according to the intention to treat principle. For the primary outcome, health-related quality of life, with 4 assessment points, linear models will be used to account for repeated measures with participant ID entered as a random effect. The primary time point of interest will be the end of the intervention phase. Group, time and group by time will be analysed as fixed effects and the baseline measure will be entered as a covariate to adjust for random baseline differences. Between group difference for the dependent outcome of chemotherapy completion (yes/no) will be analysed using logistic regression. Between group differences for the remaining secondary measures (peripheral muscle force-generating capacity, muscle mass, exercise tolerance) will be examined using linear regression with the corresponding baseline measure used as a covariate. Data transformations or alternative models (such as gamma distribution) will be considered if there is poor model fit.

Missing data will be examined and multiple imputations investigated (assuming they are missing at random). Models will be adjusted for covariates, randomisation variables and confounders such as age. Estimates of the effects will be reported with their corresponding 95% confidence intervals.

*The first secondary research question is:*

- Do factors such as adherence, treatment pathway and cancer stage moderate the magnitude of any change in primary or secondary outcomes? (i.e. moderator analysis)

To understand any moderator effects, the listed covariates will be entered into a multivariable model using the outcomes listed above. In addition, adherence will be examined to see if it mediates the relationship with the outcomes, by calculating the indirect through the use of partial coefficients.

*The second secondary research question is:*

- What is the health care utilisation, absenteeism and presenteeism over the 12 months following randomisation?

This is an exploratory question and data will be described using mean and standard deviation.

*The third secondary research question is:*

- Does performance on tests of peripheral muscle force-generating capacity and exercise tolerance, change with test repetition (i.e. is there a learning effect)?

This will be assessed using one-way repeated measures analysis of variance (ANOVA). That is, for each participant, data collected over consecutive trials (5 attempts for each measure of muscle force and 2 attempts for the 6MWT) compared to explore if there is an effect of test repetition on these outcomes.

*The fourth secondary research question is:*

What is the minimal detectable difference in health-related quality of life and exercise tolerance?

This will be assessed using anchor-based approach via a Receiver Operating Characteristic curve. This curve will determine the optimal operating point to discriminate between participants who rate themselves as changed vs unchanged at the end of the SMART program.

*The fifth secondary research question is:*

Do psychological determinants of behavioural change, such as capability, opportunity, and motivation affect adherence to the SMART program and physical activity maintenance?

This will be assessed using correlations and a Multiple Regression Analysis of the data from psychological determinant measures (COM-B factors, impairment in functioning, intention, self-efficacy, habit, and mood) across all time-points for each participant. Data from the exit interviews will also be analysed using qualitative methods (such as thematic analysis) to explore participants' reasons for engagement (or lack of engagement).

*The sixth secondary research question is:*

Does the SMART program improve mood, and does mood influence adherence to the program and physical activity maintenance?

This will be assessed using correlations between mood data from the PANAS (across all timepoints) and physical activity engagement.

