## Trial Duration/Schedule

The trial will run over a three-year period, with recruitment commencing in early 2024. Each participant will provide informed consent, after which they will complete a baseline assessment. On completion of the baseline assessments, participants will be randomised to either the experimental or control group and complete a 16-week intervention phase. Thereafter, all participants will complete a suite of re-assessments, (i) mid-way through the intervention phase, (ii) on completion of the intervention phase and, (iii) 12 months following randomisation.

| Milestones                                                           | Timeline        |
|----------------------------------------------------------------------|-----------------|
| 1. Recruit study personnel                                           | July 2023       |
| 2. Complete draft study proposal                                     | November 2023   |
| 3. Submit to ethics/governance                                       | November 2023   |
| 4. Approval obtained from all relevant HREC / RGO                    | February 2024   |
| 5. Commence recruitment (recruitment target = 15 participants/month) | March 2024      |
| 6. Commence intervention                                             | March 2024      |
| 7. Last participant recruitment                                      | March 2026      |
| 8. Complete intervention                                             | July 2026       |
| 9. Complete post-intervention assessments                            | August 2026     |
| 10. Complete long term follow-up assessments                         | March 2027      |
| 11. Data cleaning, analysis and report writing                       | From March 2026 |
| 12. Final study publications and report complete                     | September 2027  |

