## Efficacy assessment

Data collection will require two visits to the Physiotherapy Department at RPH. These assessments will be approximately 90 minutes in duration and will be completed pre-randomisation (baseline assessment) and at the end of the intervention phase. All other data collection will be done by extracting information from medical records, during phone conversations with the participants or by emailing out questionnaires through online formats (e.g. REDCap).

Table 1: Timing of outcomes

|                                                          | Pre-randomisation | Each week during the intervention phase | Mid-way through the intervention phase | On completion of the of intervention phase | 12 months following randomisation |
|----------------------------------------------------------|--------------------------|------------------------------------------------|-----------------------------------------------|---------------------------------------------------|------------------------------------------|
| Descriptive data (age, sex etc)                          | X                        |                                                |                                               |                                                   |                                          |
| EORTC QLQ C30 with BR45 (health-related quality of life) | X                        |                                                | X                                             | X                                                 | X                                        |
| EQ-5D-5L                                                 | X                        |                                                | X                                             | X                                                 | X                                        |
| Grip strength                                            | X                        |                                                |                                               | X                                                 |                                          |
| Deltoid, bicep and quads strength                        | X                        |                                                |                                               | X                                                 |                                          |

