## **Sample Size**

Sample size calculation has been conducted using the EORTC QLQ BR-30 (continuous data) as the dependent variable. To detect a difference between the experimental and control groups in this outcome of 8 (which has been estimated as the minimal clinically important difference), assuming a standard deviation of 20.52 (based on previously published literature) (Karsten 2022), with an  $\alpha = 0.05$  and  $1-\beta = 0.8$ , we will need to 104 participants in the experimental group and 104 participants in the control group. In order to account for 20% drop-out, we plan to recruit a sample size of 130 participants in each group. This means we aim to recruit 260 participants over 24 months (recruitment rate of 11 per month).

We believe that this recruitment rate is realistic. This is because, we have recently completed an audit of the RPH Breast Clinic (GEKO number 50167). The Data, Digital and Innovation (DDI) group at RPH compiled information from WEBPAS and showed that 993 adults were treated with surgical breast procedures and/or chemotherapy treatment for BC at the RPH Breast Clinic between 01/07/2021 to 30/06/2023. This is equivalent to 41 people per month. This means that our recruitment fraction for this study will be 27%.

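### As worded, the primary repeated-measures model uses the baseline score both as a response and as a covariate, and does not say which term is the week-16 test

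*Protocol*

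**What the plan says.** The Statistics and Interim Analysis section of the protocol describes the primary analysis as follows: "For the primary outcome, health-related quality of life, with 4 assessment points, linear models will be used to account for repeated measures". The model has a random intercept for each participant. On the remaining terms the section says: "Group, time and group by time will be analysed as fixed effects and the baseline measure will be entered as a covariate". The stated purpose of the covariate is to adjust for chance baseline differences. The same paragraph adds: "The primary time point of interest will be the end of the intervention phase". It does not say whether the test at that point is the group contrast at week 16 or the group-by-time term.

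Trial Duration/Schedule lists the re-assessments after randomisation: "i) mid-way through the intervention phase, (ii) on completion of the intervention phase and, (iii) 12 months following randomisation". That makes three. In the timing-of-outcomes table under Efficacy assessment, the row that begins "EORTC QLQ C30 with BR45 (health-related quality of life" has four marks: pre-randomisation and those same three visits. Four is therefore reached only by counting baseline.

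**The concern.** If four rows per participant go into the model and baseline is also a covariate, the outcome equals the covariate in every baseline row. This has two effects.

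- The common covariate slope is pulled towards 1, and the baseline residuals are artificially small. They enter the pooled variance that the model uses at every visit, so the week-16 standard error comes out too small.
- The covariate takes the same value at all of a participant's visits. It therefore drops out of any comparison between visits, and a baseline-to-week-16 group-by-time term becomes a plain comparison of change scores. On that reading the adjustment the protocol asks for has no effect.

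This is the primary analysis. Either its 95% confidence interval is too narrow, or the test has less power than a properly adjusted one. Which of the two occurs depends on a choice the protocol leaves open.

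**Working it through.** **Inputs.** From Sample Size: "To detect a difference between the experimental and control groups in this outcome of 8", "assuming a standard deviation of 20.52", alpha 0.05, power 0.80, 104 per arm, 130 after 20% drop-out. From Statistics and Interim Analysis: random intercept, four points, baseline covariate. Assumed, because the protocol gives no value: correlation ρ between visits, 0.3 to 0.8, equal for all pairs of visits, with the same SD at each visit and complete data on 104 per arm.

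**Reproducing the plan's figure.** n = 2 × (1.96 + 0.8416)² × 20.52² / 8² = 103.3, so 104 per arm. 104 / (1 − 0.2) = 130. Both agree with the protocol, with a two-sided alpha. The sample size is not in question.

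**Week-16 contrast, literal model** (variances in units of 20.52²):

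- Common slope: b = (1 + 3ρ)/4, instead of ρ.
- Variance the model assigns to a single visit: (1 − ρ) + [(1 + 3ρ)/4 − b² − (1 − ρ)/4].
- True variance of the adjusted week-16 score: 1 − 2bρ + b².
- Each standard error: 20.52 × √(2 × variance / 104).
- Type I error: 2 × [1 − Φ(1.96 × model SE / true SE)].

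At ρ = 0.5, b = 0.625. The model variance is 0.5 + (0.625 − 0.3906 − 0.125) = 0.6094, giving SE 2.22. The true variance is 1 − 0.625 + 0.3906 = 0.7656, giving SE 2.49. The ratio is 0.892 and the type I error is 8.0%.

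**Group-by-time term, baseline to week 16.** The covariate cancels and the variance is 2(1 − ρ). With baseline as covariate only, it is 1 − ρ². Power is Φ(8/SE − 1.96). At ρ = 0.5 the interaction SE is 2.85 and power is Φ(2.81 − 1.96) = 80%. With covariate only, the SE is 2.46 and power is 90%.

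| ρ (assumed) | Slope | Model SE | True SE | SE too small by | Type I error | Power, interaction | Power, covariate only |
|---|---|---|---|---|---|---|---|
| 0.3 | 0.475 | 2.50 | 2.76 | 9.3% | 7.5% | 66% | 84% |
| 0.4 | 0.550 | 2.38 | 2.64 | 10.1% | 7.8% | 73% | 87% |
| 0.5 | 0.625 | 2.22 | 2.49 | 10.8% | 8.0% | 80% | 90% |
| 0.6 | 0.700 | 2.03 | 2.29 | 11.4% | 8.3% | 88% | 94% |
| 0.7 | 0.775 | 1.80 | 2.04 | 12.0% | 8.5% | 95% | 98% |
| 0.8 | 0.850 | 1.50 | 1.71 | 12.5% | 8.6% | 99.4% | 99.7% |

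**Checks by simulation** (10,000 null and 5,000 alternative trials per setting):

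- At ρ = 0.3, 0.5 and 0.7 the literal week-16 contrast rejects a true null in 7.8%, 8.1% and 8.1% of trials. With three post-randomisation responses the figures are 5.2%, 5.1% and 4.9%.
- The simulated true SEs are 2.775, 2.486 and 2.034, so the model SE is 9.8%, 10.7% and 11.5% too small.
- With correlations that decay with time between visits (0.6, 0.5, 0.4), the literal contrast rejects in 8.3% of trials, against 5.1% with three responses.
- The interaction test keeps about 5% under equal correlation and 6.0% under the decaying pattern.
- REML fits at ρ = 0.5 give slope 0.626 and SE 2.23 for the literal model, against 0.501 and 2.48 with three responses.

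**Where the interaction test falls short of plan.** The protocol's calculation uses the unadjusted variance, 1 in these units. The interaction variance 2(1 − ρ) exceeds 1 exactly when ρ is below 0.5, so that is where power at 104 per arm drops below about 80%. For 80% power at ρ = 0.3 it would need 145 per arm, against 94 with baseline as covariate only.

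**The case against.** The strongest reply is that the authors meant baseline as covariate only. The count of four may describe how often quality of life is measured, with the next sentence giving the first measurement its role. The same paragraph treats strength, muscle mass and exercise tolerance by regression with baseline as covariate, which points the same way. That reading is possible, and it is why this is a fault in the wording and not proof that a wrong model will be fitted. But the text does not say that the baseline row is left out of the response, and an analyst who builds four rows per participant would be following it.

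A second reply is that response rows and reported coefficients belong in the statistical analysis plan, which the protocol says will be published. Leaving these out would be no finding. Here, however, the protocol does specify the model, and the specification taken literally is faulty.

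Some stronger inferences are not supported:

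- A reader might infer that the effect is diluted by averaging over four visits: (0 + 8 + 8 + 8)/4 = 6. Study Endpoints and the analysis section both fix 16 weeks as the primary time, so nothing invites that average.
- A reader might infer a type I error as high as 10%. Neither the formula nor the simulations above reach that.
- A reader might infer that baseline adjustment is lost altogether. That holds only for the interaction reading. Under the week-16 contrast the covariate still adjusts, with the wrong slope, and randomisation keeps the estimate unbiased.
- The power loss is mostly relative to a better analysis. From ρ of about 0.5 upwards the interaction test still meets the planned 80%.

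**Conclusion.** The point holds as a defect of wording in the primary analysis. Followed literally, the week-16 contrast has a standard error about 10 to 13% too small (9.3% to 12.5% by formula) and a type I error of about 8 to 9%. Its nominal 95% interval then covers about 91 to 92.5% of the time (100% minus the type I errors of 7.5 to 8.6%). If the baseline-to-week-16 interaction is tested instead, type I error is about right but power is about 66%, 80% and 95% at ρ of 0.3, 0.5 and 0.7, against 84%, 90% and 97 to 98%. These two consequences are alternatives and cannot both apply to the same test.

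The figures rest on an assumed correlation, equal variances across visits, a random intercept and complete data. The direction of the week-16 error does not depend on the value of ρ within the range shown. What cannot be concluded is that the sponsor intends the faulty model.

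**What to change.** State that the response contains only the three post-randomisation assessments (mid-intervention, 16 weeks, 12 months), with the baseline score as a covariate. Equally acceptable: keep all four assessments as responses, constrain the group means to be equal at baseline, and drop the baseline covariate. In either case, name the group contrast at 16 weeks as the primary estimate and test.

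Nothing further is needed to cure this defect. Adjustment for the randomisation variables is already in the section. A baseline-by-time term or an unstructured covariance would be a preference, since the three-response random-intercept model already holds its type I error near 5% in the settings checked.

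The cost is one or two sentences in the protocol or analysis plan, with no new data, participants or visits. It should be settled before any unblinded analysis, so that the choice of model cannot follow the results.

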### Blinding and Randomisation

Participants will be randomised (ratio of 1:1) to the experimental or control group, with computer generated randomisation using REDcap software. The randomisation sequence will be stratified for, (i) treatment pathway (chemotherapy, hormonal treatment and/or surgery), (ii) whether the person lives in Perth or outside Perth (i.e. rural or remote location) and (iii) whether the person regularly engaged in

exercise (or not) prior to their BC diagnosis. The randomisation sequence will be concealed using the REDcap software.

Data collected during all re-assessments (i.e. following randomisation) will be performed by a researcher blinded to group allocation.

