### Participant inclusion criteria

Adults will be eligible to participate if they meet the following criteria:

1. Adult with newly diagnosed breast cancer (within the last 6 months)
2. Consent to treatment for their BC, which may include chemotherapy and/or endocrine therapy

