**Exercise tolerance** will be measured as the six-minute walk test (Schmidt 2013). This test will be performed according to standard guidelines (Schmidt 2013). The outcome measured is the distance walked in 6 minutes (6MWD). Each participant will perform the test twice and the longest 6MWD will be recorded as the test result.

**Muscle mass** and body composition will be measured via bioimpedance spectroscopy. This is a non-invasive measure of body composition performed using the SOZO analyser (Impedimed, Brisbane, Queensland). The test takes under a minute, with the participant clothed and standing on the testing platform. The SOZO device is already used in standard care in patient with BC to identify the presence of lymphoedema. This device applies 256 discrete current frequencies through the body, which provides estimates of tissue composition (skeletal muscle mass, fat mass, fat free mass), fluid variables (total body water, extracellular fluid and intracellular fluid), and a metabolic report (cell health, basal metabolic rate and active tissue mass) (Kyle, et al, 2004; Grisbrook, et al, 2015).

**Chemotherapy completion rates** will be extracted from medical records and recorded as a mean relative dose intensity (RDI), which records the actual chemotherapy medication dose intensity as a fraction of the original planned dose intensity, accounting for both the dose and the number of weeks in the chemotherapy cycle (Longo 1991). Any dose adjustments or dose delays will be obtained from the medical records and/or the treating oncologist and the percent of participants requiring dose adjustments or delay will be recorded.

**Psychological determinants of behaviour change** will be measured using; (i) the Capability, Opportunity, Motivation – Behaviour (COM-B; Michie et al. 2011) model factors, (ii) impairment in functioning, (iii) intention, (iv) self-efficacy, (v) habit. These are described below:

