## **Selection of participants for analyses:**

All randomised participants will be included in the final analyses, according to the intention to treat principle.

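### Chemotherapy completion is defined as relative dose intensity but analysed as an undefined yes/no variable, in an analysis set that includes people with no chemotherapy to complete

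*Protocol*

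**What the plan says.** Section 7 (Secondary outcomes) says that chemotherapy completion rates are taken from medical records and "recorded as a mean relative dose intensity (RDI"), meaning the dose intensity delivered as a fraction of that originally planned. It adds a second quantity: "the percent of participants requiring dose adjustments or delay will be recorded".

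Section 9 (Statistics and Interim Analysis) states: "Between group difference for the dependent outcome of chemotherapy completion (yes/no) will be analysed using logistic regression". The next sentence deals with the other secondary outcomes: the "remaining secondary measures (peripheral muscle force-generating capacity, muscle mass, exercise tolerance) will be examined using linear regression". RDI is not in that list. The same section applies intention to treat, adjusts models for the randomisation variables, and says that multiple imputation will be investigated for missing data.

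On the analysis set, Section 9 (Selection of participants for analyses) says: "All randomised participants will be included in the final analyses, according to the intention to treat principle". No exception is made for this outcome.

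On who is randomised, the second inclusion criterion in Section 5 reads: "Consent to treatment for their BC, which may include chemotherapy and/or endocrine therapy". Section 4 (Blinding and Randomisation) stratifies by "treatment pathway (chemotherapy, hormonal treatment and/or surgery"). Section 5 (Source of Participants) also describes recruiting patients who finish radiotherapy before starting hormone medication.

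**The concern.** There are two separate faults. First, the quantity defined and the quantity analysed differ. The Protocol gives no RDI threshold and no other rule for completion, so the analyst must invent the yes/no variable, and the outcome as defined is never compared between groups.

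Second, the analysis set contains people who cannot have the outcome. Someone treated by surgery and endocrine therapy alone has no planned dose intensity, so RDI has no denominator and completion is neither yes nor no. Treating the value as missing and imputing it would create data for an event that could not happen.

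Chemotherapy completion is named in the second of the two primary research questions (Section 3), although it is labelled a secondary outcome. What is at stake is whether its result can be interpreted, and whether definition and denominator could be chosen after the data are seen. The primary quality-of-life comparison is not affected.

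**Working it through.** The Protocol states no sample size, completion rate or effect size for this outcome. Its 104 and 130 per group concern quality of life, so there is no plan figure to reproduce. The main check is textual.

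**Definition against model**

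| Quantity | Type | Recorded (Section 7) | Analysis (Section 9) |
|---|---|---|---|
| RDI | continuous | yes | none stated |
| Dose adjustment or delay | yes/no per participant | yes | none stated; not called completion |
| Completion (yes/no) | binary | no definition | logistic regression |

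The only quantity with an analysis is the only one without a definition.

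**Eligibility against analysis set.** Chemotherapy is optional under the inclusion criteria and is one of several pathways in the stratification, so participants without it are expected by design. The analysis set is everyone randomised. Nothing says how those without chemotherapy enter this analysis.

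**Time window.** The schedule of outcomes in Section 7 collects chemotherapy completion weekly during the intervention phase and at its end, with no entry before randomisation. Collection therefore sits after randomisation. The RDI denominator is the originally planned dose intensity, with no statement that it is limited to that period. Entry is allowed up to 6 months after diagnosis, and nothing says how a course that runs past week 16 is handled.

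**Does the denominator bias the estimate?** The inputs here are assumed, not taken from the Protocol: 65 recipients and 65 non-recipients per group, with 55/65 completing in one group and 46/65 in the other (about 85% and 71%).

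- Recipients only: OR = (55/10)/(46/19) = 2.27. SE of log OR = √(1/55 + 1/10 + 1/46 + 1/19) = 0.439.
- Everyone, unadjusted, non-recipients coded no: OR = (55/75)/(46/84) = 1.34.
- Everyone, unadjusted, non-recipients coded yes: OR = (120/10)/(111/19) = 2.05.
- Everyone, adjusted for a pathway factor that separates recipients from non-recipients exactly: in the non-recipient stratum every outcome is the same, the stratum intercept goes to plus or minus infinity, and its log-likelihood contribution goes to zero whatever the treatment coefficient. The estimate is the recipients-only one, OR 2.27 with SE 0.439, under either coding.

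The coding thus matters in an unadjusted comparison, or where the strata do not separate the two kinds of participant cleanly. It does not matter under full separation with the planned adjustment.

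**The case against.** The best defence has four parts.

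- **Adjustment removes the dilution.** A reader might infer that including non-recipients shrinks the treatment effect in proportion to their share. The documents do not support that as a general statement. Section 9 adjusts for the randomisation variables, pathway is one of them, and the arithmetic above shows no dilution when pathway separates recipients from non-recipients. Dilution remains possible only without adjustment or with imperfect separation. The and/or wording of the pathway factor leaves separation uncertain.
- **Something collected does fit the model.** A reader might conclude that nothing recorded can enter a logistic regression. That goes too far: dose adjustment or delay is a per-participant yes/no, and RDI could be cut at a threshold. What stands is that neither is identified as completion.
- **The statistical analysis plan can supply the cut-off.** It can, and Section 9 says that a final plan will be published. A cut-off would define the yes/no variable, but would still leave RDI itself unanalysed and would not change the explicit statement that all randomised participants are analysed.
- **Miscoding is hypothetical.** The Protocol does not say that people without chemotherapy will be coded yes or no, and its intention-to-treat sentence is general. That is fair. The fault is that the denominator for this outcome is not stated and the general rule, taken literally, includes them.

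It is also tempting to quote a percentage of information lost by dichotomising. The usual figures assume a normal outcome. RDI is likely to pile up near 1, so they do not apply and none is given here.

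**Conclusion.** The point holds as a contradiction between the definition in Section 7 and the analysis in Section 9, together with an analysis set that includes people for whom the outcome does not exist. Both follow from the text and need no assumption.

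No numerical size can be attached from the documents. In the assumed example the odds ratio is 2.27 in recipients and 1.34 or 2.05 in an unadjusted analysis of everyone, depending on the coding. It stays at 2.27 under the planned adjustment if pathway fully separates the groups. That is a range of possibilities, not an estimate of bias in this trial.

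This should be corrected before analysis. It concerns one secondary outcome and leaves the primary endpoint untouched.

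**What to change.** Use one definition in Sections 7 and 9, and state the analysis set.

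- **Outcome:** RDI over the doses planned after randomisation, which agrees with the existing collection schedule. State how courses running past week 16 are handled.
- **Analysis:** treat RDI as continuous, adjust for the stratification factors, and use robust or bootstrap confidence intervals because values are likely to gather near 1.
- **Analysis set:** randomised participants with chemotherapy planned or still remaining at randomisation, kept in their allocated groups. Identify them from treatment records that predate randomisation, because the pathway stratum alone does not show remaining cycles. Selecting on pre-randomisation information preserves the randomised comparison.
- **Supportive analysis:** any dose adjustment or delay (yes/no) in the same set by logistic regression, replacing the undefined completion variable.
- **Missing data:** limit any imputation of this outcome to members of that set.

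The cost is revised wording and a check of remaining cycles at baseline; the outcome data are already to be extracted from medical records. The downside is a smaller denominator. If 75%, 50% or 30% of 130 per group had chemotherapy (assumed shares), the set would be about 98, 65 or 39 per group. The people left out carry no information on this outcome, so the smaller number describes the evidence more honestly.
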